## II. SPECIFIC AIMS

The present proposal is based on qualitative formative work, an open pilot of the face-to-face 3RP-NF, and a pilot single blinded RCT of the 3RP-NF versus HEP-NF, both delivered via videoconferencing with Skype showing feasibility, acceptability, preliminary efficacy and durability. The objective of the study is to test, within a single blinded fully powered RCT, the efficacy of the 3RP-NF as compared to HEP-NF (attention control) in improving co-primary (physical and psychological quality of life) and secondary (social quality of life, environmental quality of life, depression, anxiety, pain intensity and pain interference) outcomes. **Specific aims:**

- Aim 1:** to determine the efficacy of 3RP-NF in comparison to an active control HLI on the co-primary outcomes: physical health QOL and psychological health QOL among patients with NF1, NF2 and schwannomatosis. Secondary outcomes are: social relationships QoL, environment QoL, depression, anxiety, pain, pain interference, gratitude, optimism, mindfulness, coping, social support, empathy and stress. Assessments will be conducted at baseline, post-intervention (8 weeks, primary time point), 6 and 12 months follow-ups (secondary time points). Both intervention and control are delivered via live video with Zoom.

**Hypotheses:** 3RP-NF will be more efficacious in reducing primary and secondary outcomes at post-intervention, and effects will be maintained at 6 and 12 months follow-ups, compared to HEP-NF.

- Aim 2:** to examine the degree to which treatment-dependent improvements in the primary outcomes are mediated by improvements in depression, anxiety, pain intensity, pain interference, gratitude, optimism, mindfulness, coping, social support, empathy and stress (conceptual mediators) and modified by NF type, age, race/ethnicity, learning disability and education level.

**Hypotheses:** Treatment-dependent improvements in the secondary outcomes depicted in the figure below will mediate benefits from 3RP-NR for the primary outcomes. The moderators NF type, age, and race/ethnicity will be associated with differential benefit from 3RP-NF for the primary outcomes.

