post-intervention) and durability (to 6 and 12 months) of the 3RP-NF. Accordingly, the primary analysis will compare changes in primary and secondary outcomes (continuous measures) from baseline to the post-, 6 months and 12 months visits between the randomized conditions. All randomized participants will be included in our primary efficacy analyses as randomized, following the intention-to-treat principle. Data will be analyzed using a shared-baseline, linear mixed model with fully unstructured covariance among repeated measures. The shared-baseline assumption reflects the true state of the population prior to randomization and has the benefit of adjusting for chance differences at baseline. For each outcome, we will compare the effect of 3RP-NF vs. HEP-NF on changes from baseline to the post-test, 6 and 12 months follow-up times using linear contrasts. Our primary aim will focus on the post-treatment follow-up time. With two co-primary outcomes, we will use two-sided tests at  $p < 0.025$  to declare superiority of 3RP-NF, maintaining an overall 5% type 1 error at our primary post-intervention time point. Persistence of a benefit from 3RP-NF at 6 and 12 month follow-up times will be analyzed as a non-inferiority test of durability. Non-inferiority of 3RP-NF in maintaining benefits relative to HEP-NF will be declared if the lower one-sided 95% confidence bound for a given co-primary outcome is less than 6.25 units (the estimated MCID) in favor of HEP-NF. Several sensitivity analyses will be explored using alternative models. Change scores at post-intervention, 6 months, and 12 months will be separately analyzed by Wilcoxon rank sum test to avoid any parametric assumptions about the data. More parsimonious covariance structures will be considered using random participant-specific intercepts, slopes, and quadratic terms (i.e., growth curve analysis). Baseline parameters such as NRS pain will be included to account for chance differences due to randomization and to explain sources of variation in response that are independent of treatment group.

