While no information on clinically meaningful differences exists for the primary outcome measures for patients with NF, we will also use both “distribution-based” and “anchor-based” methods as criteria to determine important change. Consistent with “anchor based” methods, we will ask patients at post-treatment, 6 and 12 months follow ups to rate whether they were “substantially better”, “minimally better” “about the same”, “minimally worse” or “substantially worse” as compared to how they were before the intervention. These improvement ratings would thus serve as the standard with which to evaluate the importance to the patient of whatever changes in quality of life occurred during the intervention. Success of the trial will thus be estimated based on outcome score (quality of life scores) and anchor-based measures of subjective improvement. The anchor-based MCID estimates will be computed using prior methodology, as the mean change in the physical health and psychological health QoL among those in the “minimally better” category.

**3.1. Power Consideration and Sample Size Calculations.** The effective standard deviation (SD) for the change from baseline to post-treatment in QoL Physical and QoL Psychological based on a repeated-measures ANOVA of our preliminary data was 14.7 and 10.4 units, respectively. The effective SD from post-treatment to 6-month follow-up was 11.4 and 10.0 units, respectively. Based on these estimates, assuming an MCID of 6.25 units, allowing up to 5% loss to follow-up by post-treatment assessment, and testing each of the co-primary outcomes at  $p < 0.025$  two-sided, the study will have 80% power for QoL Physical and 96% power for QoL Psychological. Allowing up to 20% loss to follow-up by the 6-month assessment, the study will have 99% power to declaring non-inferiority of 3RP-NF vs. HEP-NF if the true treatment-dependent difference in maintenance of any change from baseline to post-treatment is zero.

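### The durability rule allows a relative loss as large as the whole target effect and does not require that a benefit was ever shown or remains at follow-up

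*Protocol*

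**What the plan says.** Aim 1 (section II) hypothesises that "effects will be maintained at 6 and 12 months follow-ups, compared to HEP-NF". Section VI.3 makes this operational: "Persistence of a benefit from 3RP-NF at 6 and 12 month follow-up times will be analyzed as a non-inferiority test of durability". Success is declared separately for each co-primary outcome if the "lower one-sided 95% confidence bound for a given co-primary outcome is less than 6.25 units (the estimated MCID) in favor of HEP-NF".

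The same section describes the general model contrasts as comparing arms on "changes from baseline to the post-test, 6 and 12 months follow-up times using linear contrasts". It does not repeat which contrast the durability bound applies to.

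Section VI.3.1 powers superiority at post-treatment "assuming an MCID of 6.25 units", at two-sided 0.025 per outcome. It gives SDs for the change from post-treatment to 6 months of 11.4 (Physical) and 10.0 (Psychological), and states 99% power for durability "if the true treatment-dependent difference in maintenance of any change from baseline to post-treatment is zero".

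**The concern.** A durability claim has two parts: there was an advantage over HEP-NF, and a worthwhile share of it is still there. The rule tests neither directly. It asks only that 3RP-NF has not lost more than 6.25 units relative to HEP-NF, and 6.25 units is all the benefit the trial expects to produce. It is also not conditional on the post-treatment result. If the two arms never differ, there is nothing to lose and the rule is met almost automatically.

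At stake is the second half of the Aim 1 hypothesis. A trial could report that a benefit persisted to 6 or 12 months when none was shown, or when much of a real one had gone.

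**Working it through.** **Inputs (Protocol).** 224 enrolled 1:1; at least 212 at post-treatment (106 per arm) and 180 at 6 and 12 months (90 per arm), from VI.1. Margin 6.25 and one-sided 5%, from VI.3. Target effect 6.25, two-sided 0.025, and SDs from VI.3.1: baseline to post-treatment 14.7 / 10.4; post-treatment to 6 months 11.4 / 10.0 (Physical / Psychological).

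**Formula.** With SE = SD × √(2/n) and a normal approximation,

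P(declare durable) = Φ((6.25 − true relative loss)/SE − 1.645).

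SE at 90 per arm: 11.4 × √(2/90) = 1.70 (Physical); 10.0 × √(2/90) = 1.49 (Psychological).

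**Step 1. The protocol's own figure.** At zero loss:
- Physical: Φ(6.25/1.699 − 1.645) = Φ(2.03) = 97.9%.
- Psychological: Φ(6.25/1.491 − 1.645) = Φ(2.55) = 99.5%.

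This agrees with the stated 99% to within about one percentage point, so that figure fits a one-sided 5% test on the post-treatment-to-6-month change.

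**Step 2. No effect at any visit.** If 3RP-NF never differs from HEP-NF, the true difference in maintenance is also zero. The calculation is the same as in step 1: durability is declared 97.9% / 99.5% of the time. The stated power therefore describes an ineffective treatment equally well.

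**Step 3. A true benefit that is partly or wholly lost.**

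| True relative loss | Physical | Psychological |
|---|---|---|
| 3.125 (half of 6.25) | Φ(3.125/1.699 − 1.645) = 57.7% | Φ(3.125/1.491 − 1.645) = 67.4% |
| 6.25 (all) | 5% | 5% |

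**Step 4. Largest observed loss that passes.** 6.25 − 1.645 × SE gives 3.45 units (55% of 6.25) for Physical and 3.80 units (61%) for Psychological.

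**Step 5. Would a superiority gate alone be enough?** The smallest observed post-treatment difference significant at two-sided 0.025 is 2.241 × SE at 106 per arm.
- Psychological: 2.241 × 10.4 × √(2/106) = 3.2 units. This is below 3.80, so a just-significant benefit could disappear entirely in the observed data and still be called durable.
- Physical: 2.241 × 14.7 × √(2/106) = 4.5 units. This is above 3.45, so the same cannot happen at these SDs.

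A gate on post-treatment superiority removes the case in step 2 but not this one.

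**Step 6. Power of a superiority test at 6 months.** The protocol gives no SD for baseline to 6 months, so a range is assumed. The lower end carries the baseline-to-post-treatment SD forward (14.7 / 10.4). The upper end treats the two intervals as independent: √(14.7² + 11.4²) = 18.6 and √(10.4² + 10.0²) = 14.4. For a persisting 6.25 units, 90 per arm and two-sided 0.025, power = Φ(6.25/SE − 2.241).
- Physical: 73% (SD 14.7) down to 50% (SD 18.6).
- Psychological: 96% (SD 10.4) down to 75% (SD 14.4).

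**The case against.** The strongest defence has four parts.

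**The wording presupposes a benefit.** Section VI.3 speaks of persistence and of maintaining benefits, so a sensible analyst would not claim durability after a failed superiority test. The between-arm contrasts at 6 and 12 months will also be estimated, so an absent benefit would be visible. This lowers the practical risk. But the declaration rule contains no such condition, and section VI.4.1 shows that the protocol writes one where it wants one: mediation is explored only if the intervention shows improvement. A later analysis plan may add detail, but the margin, confidence level and decision rule are already fixed here.

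**6.25 is the MCID.** A relative loss below it is by definition unimportant to patients, and the pilot (section I, Study 5) used the same threshold. This is a legitimate choice for judging how much loss matters. It does not show that a benefit persists when the expected benefit is the same 6.25 units. A particular smaller margin has no source in the protocol either, so none is proposed.

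**The contrast is clear enough.** A reader might infer that the bound applies to change from baseline, so that zero advantage at follow-up would usually pass. The durability SDs, the power statement and the pilot's definition all point instead to the post-treatment-to-follow-up change. The baseline reading would also need SDs that the protocol does not give. The results here do not rest on it; the protocol should simply name the contrast.

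**Error level.** A reader might see the one-sided 5% level as contradicting the stricter level used for superiority. It does not, because section VI.3 claims overall 5% control only at the post-intervention time point.

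**Conclusion.** The point holds and should be fixed. As written, the rule can support a conclusion of persistent benefit about 98% (Physical) and 99% (Psychological) of the time when there was no effect at any visit, and 58% and 67% of the time when half of a 6.25-unit benefit is truly lost. For Psychological QoL, a just-significant benefit of about 3.2 units could vanish and still pass.

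Two stronger readings are not supported. The rule does not always pass a true half loss; it does so more often than not. Nor does it readily pass the disappearance of a full 6.25-unit benefit, which succeeds only 5% of the time.

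The figures rest on about 90 per arm at follow-up, the protocol's 6-month SDs and a normal approximation. No 12-month SD is given, so carrying them to 12 months assumes the same SD. The follow-ups are secondary time points; the post-treatment superiority test, its error control and the sample size are not affected.

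**What to change.** In VI.3, for each co-primary outcome, claim durability only if:

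1. superiority was declared at post-treatment for that outcome; and
2. 3RP-NF is superior to HEP-NF on the baseline-to-6-month contrast and then on the baseline-to-12-month contrast, tested in that order at the outcome's two-sided 0.025 level.

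The planned mixed model already estimates both contrasts. Keep the 6.25-unit bound as a supportive analysis and state that it applies to the change from post-treatment to follow-up.

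In VI.3.1, replace the 99% durability power with the power of the new rule, and state the SD assumed for baseline to follow-up.

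The cost is wording and a less favourable power statement, with no new patients or data. For a persisting 6.25 units, the 6-month step alone has roughly 50–73% power for Physical and 75–96% for Psychological under the assumed SD ranges. The full sequence, which also needs the post-treatment gate and the 12-month step, has less. That is a real loss, but the resulting claim would match the Aim 1 hypothesis.

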#### **Study 5: [name], Riklin E, Merker V, Macklin E, Park E, Plotkin SR. Mind body therapy via videoconferencing in patients with neurofibromatosis; An RCT. Neurology, 2016.**

**Overview:** This was a single blind RCT pilot study of the 3RP-NF delivered via videoconferencing with Skype, in adults with NF1, NF2 and schwannomatosis, providing primary preliminary data for this application. The transition from face to face to Skype delivery of the intervention was done to improve feasibility and generalizability of the intervention. Patients were recruited through the CTF outreach via a flyer asking for interest in participation in a stress management study. Patients who met inclusionary and exclusionary criteria, including reports of difficulties coping with stress and NF symptoms at intake, were randomized to the 3RP-NF focused on teaching the elicitation of the relaxation response, adaptive thinking and positive psychology tools, or the Health Enhancement Program for NF attention placebo control (HEP-NF) focused on providing educational information on stress, NF, and lifestyle behaviors such as healthy eating, exercise, and sleep hygiene. Both groups were delivered online via videoconferencing with Skype. Participants were blind to the group assignment (intervention versus control). Participants from both groups received the same amount of support from the interventionist and other group members for the duration of the groups. All participants received a patient manual. Those in the 3RP-NF also received a CD that included mindfulness meditation exercises practiced during the group. Data was collected using the REDCap data management system. Patients in both groups completed homework. **Results:** The first 65 potential participants were screened for participation and 63 entered the study, completed consent, provided baseline and were randomized (32 intervention, 31 control). Of these, 63 completed the intervention (at least 6 sessions attended) and provided post-test data (32 in the 3RP-NF and 31 in the control). Of these, 53 provided 6 months follow up data. The abundance of inquiries, 100% post-test completion rate, and 82.5% 6-month follow-up completion rate indicates excellent feasibility and compliance. Satisfaction with participation in the program was high and similar at both post test and 6 months follow up between the 3RP-NF (4.19 and 3.92 out of 5) and the HEP-NF (4.10 and 3.79 out of 5) groups suggesting high acceptability and usability. The similar scores on satisfaction with both 3RP-NF and HEP-NF also suggest that blinding was maintained both at post test and 6 months follow up. Participants were middle-aged (mean±SD 43±years) and predominantly female (73%), college educated (60%), employed (73%), US-based (90%), and diagnosed with NF1 (71% NF1, 19% NF2, 10% schwannomatosis). There were no significant differences in baseline outcome variables between those randomized to 3RP-NF versus HEP-NF except for Psychological QoL, where patients in the HEP-NF had more impaired scores compared to those in the 3RP-NF ( $P < .05$ ). This is considered a chance finding given the lack of significant baseline difference in the other 7 outcome measures. A mixed methods repeated measures ANOVA following intent to treat principles was employed for the data analyses. For primary (Physical Health QoL and Psychological QoL) and secondary (social relations QoL, environmental QoL, depression, anxiety, pain intensity for those with pain higher than 4, and pain interference for those with pain higher than 4) variables we compared the effect of the 3RP-NF versus HEP-NF on changes from own baseline to post-test, and from post-test to 6 months follow-up times using linear contrast. For primary outcomes, improvement from 3RP-NF from baseline to post test was considered clinically meaningful if the mean improvement was higher than the MCID of 6.25. For primary outcomes, durability was established if there was a less than 6.25 decrease in scores from post-test to follow up. Information on minimal clinically important difference (MCID) for the study variables does not exist in patients with NF. In patients with breast cancer, distribution- and anchor-based methods suggested an MCID of 1 on a 4-20 scale for the physical and psychological domains of the WHOQOL-100^33. Extrapolated to the 0-100 scale used for WHOQOL-BREF subscales, this is equivalent to 6.25 units. This value was used to indicate meaningful change for the primary variables. Patients in the 3RP-NF showed greater improvement in Physical Health QoL (7.69; 95% CI: 0.29-15.10;  $P = .040$ ), Psychological QoL [5.57; 95%

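### The printed baseline-to-post SD of 10.4 for QoL Psychological gives neither the stated 96% power nor the pilot P value it is said to come from; both point to about 11.4

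*Protocol*

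**What the plan says.** Protocol VI.3.1 takes its planning SDs from a repeated-measures ANOVA of the preliminary data. With Physical named before Psychological in each pair, the SD of change to post-treatment "was 14.7 and 10.4 units, respectively. The effective SD from post-treatment to 6-month follow-up was 11.4 and 10.0 units" for the later interval.

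The calculation is described as "assuming an MCID of 6.25 units, allowing up to 5% loss to follow-up by post-treatment assessment". Each co-primary outcome has its own two-sided test at 0.025. The result is that "the study will have 80% power for QoL Physical and 96% power for QoL Psychological". For durability, with up to 20% loss by 6 months and a true difference of zero, "the study will have 99% power to declaring non-inferiority". That last figure is given once, without naming an outcome.

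VI.1 (Missing data) gives the numbers: 224 enrolled, at least 212 at post-treatment and 180 at 6 and 12 months. Section V gives 1:1 randomization. Section VI.3 gives the non-inferiority margin of 6.25 units and a one-sided 95% bound.

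The pilot is Study 5 in Section I, with post-test data on 32 and 31 participants. The between-arm differences in change to post-test were 7.69 for Physical (95% CI 0.29 to 15.10, P=.040) and 5.57 for Psychological (CI printed as 0.17 to 11.34, P=.056).

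**The concern.** The two post-treatment powers share every input except the SD, so one method should return both. It returns the Physical figure and misses the Psychological one. The SDs are also said to come from a pilot whose estimates and P values are printed in the same Protocol, so they can be checked at source, and 10.4 fails that check too.

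QoL Psychological is a co-primary outcome. As printed, a reader cannot reproduce its power. Anyone who reuses 10.4 (to allow for the therapy groups or for higher attrition, say) would start from a variance about 17% too small if 11.4 is the right value: (10.4/11.4)² = 0.83.

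**Working it through.** **Inputs.** Difference 6.25, two-sided alpha 0.025, and the printed SDs (VI.3.1); 212 evaluable, hence 106 per arm at 1:1 (VI.1, V); pilot results and arm sizes (Section I, Study 5).

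**1. Power at post-treatment.** Power = Φ(6.25 / (SD × √(2/106)) − 2.2414), with √(2/106) = 0.13736.

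| Outcome and SD | SE | 6.25/SE | Power, normal | Power, t | Stated |
|---|---|---|---|---|---|
| Physical, 14.7 (printed) | 2.019 | 3.095 | 80.3% | 79.8% | 80% |
| Psychological, 10.4 (printed) | 1.429 | 4.375 | 98.4% | 98.2% | 96% |
| Psychological, 11.4 (trial value) | 1.566 | 3.991 | 96.0% | 95.8% | 96% |

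The Physical row reproduces the plan's figure and so confirms the method. Solving for 96% gives an SD of 11.3 (t) to 11.4 (normal).

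**2. Could other inputs give 96% with SD 10.4?** Two do. Using 90 per arm gives 96.1% to 96.3%, and alpha 0.01 gives 96.1% to 96.4%. The first contradicts the stated 5% loss and the second the stated 0.025. They would also put Physical at 72% to 73% and 69% to 70% respectively, not 80%.

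**3. The pilot as source.** For 32 vs 31, √(1/32 + 1/31) = 0.2520; with 61 df, t(0.975) = 1.9996.

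- Physical, from the CI: half-width (15.10 − 0.29)/2 = 7.405; SD = 7.405/(1.9996 × 0.2520) = 14.69. This is the printed 14.7, so the effective SD can be recovered this way. From P=.040 it is 7.69/(2.0986 × 0.2520) = 14.54, which shows that the P-value route is good to about 1%.
- Psychological, from P=.056: t = 1.9482; SD = 5.57/(1.9482 × 0.2520) = 11.35. Rounding of P allows 11.32 to 11.37.
- Psychological, in reverse: SD 10.4 gives SE 2.621, t = 2.125, P=.038. SD 11.4 gives SE 2.873, t = 1.939, P=.057. The reported value is .056.
- Psychological, from the CI as printed: half-width (11.34 − 0.17)/2 = 5.585; SD = 11.08. This interval is doubtful, because it excludes zero although P=.056, and its midpoint is 5.755 rather than 5.57. With a lower limit of −0.17 the half-width is 5.755, the midpoint 5.585 and the SD 11.42. The case does not need that reading: neither version gives 10.4.

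**4. Durability.** Power = Φ(6.25 / (SD × √(2/90)) − 1.6449), with 90 per arm, one-sided 5% and a true difference of zero.

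| SD | Power | Stated |
|---|---|---|
| 11.4 (printed, Physical) | 97.9% | 99%, outcome not named |
| 10.0 (printed, Psychological) | 99.5% | 99%, outcome not named |

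The single 99% therefore does not describe the Physical outcome at the printed SD. It is close for the Psychological one.

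**The case against.** The strongest reply is that nothing turns on this. The stated 96% is lower than the printed SD implies, so the text does not overstate power. The gap is 2.4 points. If the SD should read 11.4, the stated 96% is right and only one digit is wrong. The sample size rests on Physical at SD 14.7, which reproduces. All of this stands, and it limits the point to a correction of the planning inputs. It does not remove the point, because the printed SD still conflicts with the stated power and with the pilot result.

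A reader might go further and infer that 10.4 and 11.4 were transposed, so that the second pair should read 10.4 and 10.0. The swap is tidy: SD 10.4 at 90 per arm gives 99.1% non-inferiority power for Physical. The documents do not establish it. The 99% is not tied to Physical, the printed 10.0 for Psychological already gives 99.5%, and Study 5 reports no CI or P value for the post-test to 6-month contrast against which 11.4 could be checked. A one-digit slip in the first pair fits the evidence equally well.

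A reader might also cite the pilot CI as separate proof of 11.4. It gives 11.4 only if its lower limit is read as −0.17; as printed it gives 11.1. The P value carries this part of the argument.

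**Conclusion.** The point holds for one number. The baseline-to-post SD of 10.4 for QoL Psychological is inconsistent with the stated 96% power (it gives about 98%) and with the pilot's 5.57 and P=.056 (which imply 11.3 to 11.4). This rests on a two-sample comparison with 106 per arm, which reproduces the Physical figure, and on about 61 df for the pilot contrast, which reproduces the Physical SD from its CI.

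The post-to-6-month SDs are unverified; they have not been shown to be wrong. The fault there is that one 99% is quoted for two outcomes whose printed SDs give 97.9% and 99.5%. A swap of 10.4 and 11.4 is a possible explanation, no more. N=224, the alpha split and the margin are unaffected. This is a minor but definite error in the power section.

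**What to change.** Check the four SDs in VI.3.1 against the pilot model output.

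- If the Psychological baseline-to-post SD is 11.4, correct it; the 96% then stands.
- If 10.4 is confirmed, restate the power as 98% and explain why it differs from the SD implied by the pilot P value.
- Confirm or correct 11.4 and 10.0 for post-treatment to 6 months, and give the non-inferiority power by outcome. With the printed SDs that is 97.9% for Physical and 99.5% for Psychological.

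The cost is one look at existing output and an edit to one paragraph. Enrolment and the analysis do not change.
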